**Figure 6. TWMB Implementation and TWMB Adherence Definitions**

|                                  |   |                                                                                                                                                                                                                                                                      |
|----------------------------------|---|----------------------------------------------------------------------------------------------------------------------------------------------------------------------------------------------------------------------------------------------------------------------|
| TWMB Implementation       | = | $\frac{\text{WCC Visits for 4 to 36 months of age with acceptable TWMB adherence}}{\text{Total WCC Visits for children 4 to 36 months of age}}$                                                                                                                      |
| Acceptable TWMB Adherence |   | 
Completion of 75% of TWMB Checklist Components
 
 
Modeling Talking
 
Sharing Education
 
Encouraging Practice
 
Giving Language Nutrition Prescription
 
 |

## 8.1.2 CAREGIVER ASSESSMENTS AND PROCEDURES

### ENROLLMENT

Enrollment will occur at infant age zero to nine months (+ 0-30 days) at Week 1. (The study team will include children less than 1 month of age but will not begin data collection (LENA) until the child is 2 months of age. The study team will include children 9 months plus up to 30 days but will not include children who have turned 10 (ten) months of age.) If caregivers are unreachable at first contact for recruitment/consent (see Section 10.1.1), the study team will follow up with additional outreach attempts (at least two additional attempts).

The site study team will complete screening surveys with caregiver participants. These surveys will ask for caregiver's contact information (name, phone number(s), physical address, email address, preferred contact method) and demographics (e.g., age and race/ethnicity). For the child participant, the child's parent/guardian will be asked to provide the child's name, race/ethnicity, primary care physician, primary caregiver(s) for child, and date of birth. These surveys will also ask about the availability of internet access and smartphones that participants could use for study-related communication.

Study staff will:

1. Send caregivers an electronic link (by email or text, depending on caregiver preference and what is allowed by local IRB) to complete consent and demographics questionnaires.
2. Complete the questionnaires with caregivers in person or by phone, or
3. Send by United States Postal Services or other standard document delivery services
4. Any combination of the above.

Research staff will follow up with reminders for completion (after initial invitation). These methods (which we have used successfully in previous large-scale longitudinal studies) are feasible given national data indicate 85% of adults have smartphones (77% have broadband).

Other recruitment, screening, and enrollment procedures for caregiver-child participants are described in Section 5.1.2. As part of recruitment, the study team will maintain a Recruitment/Screening Log, as described in Section 5.5.2.1.

#### TRACKING WCC ATTENDANCE AND TWMB INTERVENTION DURING WCC

Child-caregiver dyads will receive TWMB during their WCC visits, as described in Section 6.1. The site study team will track their WCC attendance using the clinic schedule of WCC visits, as described in Section 5.5.2.1. This tracker will include scheduled appointments and attended appointments, as follows:

1. Identify and log child who attended a WCC during the past week.
2. Log visit details including the WCC provider.

#### PRIMARY ENDPOINT: CAREGIVER LANGUAGE-PROMOTION BEHAVIORS (LENA)

Caregivers will complete *LENA* recordings at Baseline (Week 1) and Post-Intervention (Week 48). *LENA*, the research standard for measuring talk with children, provides a quantitative measure of the HLE. *LENA* uses a small recorder (“talk pedometer”) children wear in a vest pocket for a day at a time (See **Figure 7**). It meets US and international safety standards, does not transmit, and has the same low-power processors as hearing aids. *LENA* software processes the audio into talk data (with built-in fidelity measures).

The *LENA* recording system, i.e., *LENA SP*, that will be used for this study allows – depending on the installation process - for recordings (“.wav” audio files) to be downloaded to local computer systems. In order to prevent actual audio (.wav) files from being downloaded or retained for this study, the site’s Information Technology (or equivalent) department will install the *LENA Hub* on the sites’ computer(s) and the installation will be tested to ensure that files cannot be downloaded or retained. No one can listen to files that have not been downloaded or retained. The specifics for this set-up and testing will be provided in either the study-specific MOP or a specific document for *LENA* set-up and testing. *LENA* corporation email(s), which will provide additional information about the *LENA SP* system, are being submitted as a separate document for UAMS IRB review. In summary, the actual words spoken by the child and family will NOT be downloaded or kept by the site, the DCOC, or *LENA* corporation and no one will be able to listen to the audio files.

The sites will complete appropriate pre-enrollment testing of the *LENA* process with volunteers who will not be eligible to be TWMB study participants. This pre-enrollment testing will include (1) setting up the sites computers as noted above and completing that computer set-up testing, (2) sending *LENA* devices to at least 1 – but not more than 4 - volunteer families per site, (3) having the volunteer families complete the in-home *LENA* procedure as specified below in this section of the protocol, (4) having the *LENA* device sent back to corresponding site, (5) having the site process the recording to ensure the uploading and processing works as intended and the words cannot be accessed by anyone. No identifiable information will be kept about the volunteers and the information from the pre-enrollment testing will not be generalizable knowledge. If requested by the cIRB, a short informed consent will be provided for the volunteers so that they are fully

informed that their conversations will be recorded but that those recordings will not be used other than to ensure the process is ready for use and works as intended. They will be informed that neither LENA nor the study personnel will be able to listen to their actual words.

**Figure 7. LENA “Talk Pedometer” Recorder and Vest With Instructions**

[figure not shown]

LENA is the research standard for measuring talk with children because it is user-friendly and widely used in the field to successfully collect data from families of diverse characteristics. Since the technology became available in 2008, LENA data have been published in 150+ observational and interventional studies involving many hundreds of children. LENA is family-friendly and has been used successfully in many large-scale studies with infants and toddlers using the methods we will use.

Study staff will mail the LENA recorder and vest to the family; alternatively, the LENA recorder may be provided to the family at a clinic visit. Study staff will then complete a short phone call with the family to walk through how to use the device and answer any questions (simple instructions are also provided with the device, see **Figure 7**). If the family opts for electronic communications, the family will get an electronic link and be able to complete the review and questionnaire electronically. Families will be asked to complete 2 day-long recordings during a period when the child is in the home setting (i.e., not at daycare), turning on and putting on the device at the start of the day when the child first wakes up and leaving it on for 12-16 hours. The LENA recorder can remain turned on and be taken off and left nearby during bath or naps, if needed. The device automatically turns off when the maximum recording time is reached. Families will be asked where the recording was obtained. Families will complete a recording on two separate days during Baseline (i.e., Phase 1); Phase 2 participants will complete a recording on two separate days again during the Post-Intervention Assessment phase.

Participants will be asked to complete questionnaires at the end of each recording day. These questionnaires will ask about where the child was (based on 2-hour intervals) during the recording time period, what the child was doing, and who was with the child during the recording time period. A paper version of the question will be sent with the LENA device. The adult participant will have the option to answer the questions electronically, by phone, or by sending the completed paper questionnaires back with the LENA devices (see below).

After completing the Baseline recording, the family will mail (includes USPS, UPS, FedEx, and other reputable delivery services) the LENA recorder and vest back to the study team in a prepaid mailer or drop the device off

at the clinic. Phase 2 participants will complete the same process during the Post-Intervention Assessment phase. Completion of LENA recordings by mail has been done successfully in previous large trials.

Site study staff will download the recording from the device to LENA's speech recognition software, which automatically analyzes the data into counts and percentiles for adult words and conversational turns. LENA captures clear adult words spoken near the child wearing the LENA recorder and is highly accurate in terms of agreement with human identification (82, 76, 71, and 76% for adult, child, television, and other speech, respectively).

The LENA software provides a fidelity and quality indicator for the data recording. LENA software provides the following quality errors to indicate an unusable recording:

- Too much overlapping noise to detect audio sample (as determined by LENA software).
- Recording too short for processing (less than 5 hours of recording time).
- Not enough child or adult speech to process (as determined by LENA software).

If the received recording does not meet LENA fidelity benchmarks to extract a usable recording, the site study team will send the LENA device back to the family in a second attempt to collect an additional sample. The site study team will enter LENA standard scores at Baseline and Post-Intervention assessments in the study database (see **Figure 8** for example LENA output), which will be used for primary outcome data, including:

- Daily **Adult Word Count (AWC)** directed to the child.
- Daily **Conversational Turn Count (CTC)** between the adult and the child.

The LENA age-referenced normative data are based on the LENA Natural Language Study, which included a large and diverse sample of children 2 to 48 months of age and their caregivers. AWC does not vary as a function of child age, so the normative data include a single mean and standard deviation for two to 48 months of age. CTC mean and standard deviation increase with age up to 25 months, then remain steady through 48 months, so the normative data include monthly intervals from two to 25 months of age.

Complete LENA data will be defined as follows: at least one usable recording (i.e., usable recording from one day of the two possible recording days) is collected from caregiver participants within two attempts (to account for potential errors in recording) at Post-Intervention.

We will monitor completeness/usability of LENA throughout baseline data collection to optimize our strategies for collecting follow-up data. Many studies using LENA have obtained 100% usable data at baseline, with other studies reporting a range of 70–100% usable data. In our own lab, we have obtained 93% usable LENA data with underserved and low-SES populations. Usable data includes compliance with wearing the LENA vest and adequate length of recording time. We will ensure caregiver understanding of LENA recording procedures by sending a LENA “how-to” video and written/visual instructions to caregivers and by completing a follow-up phone call to walk caregivers through using LENA, check for caregiver understanding of instructions, and answer any questions (see detailed procedures in the study-specific MOP). We will track reasons for unusable data.

If data usability obtained in TWMB at Baseline drops below 70%, we will conduct a root-cause analysis and present a plan for correcting the problem to the DSMB. If the source of unusable data could not be corrected, we will re-evaluate our plan to collect LENA at Post-intervention.

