The pre-post intervention design allows us to evaluate participant completion of critical measures that will be used in the future, large-scale RCT. Importantly, it also allows us to estimate expected change in caregiver language-promotion skills in response to the intervention. Since TWMB targets caregiver language behaviors, the design includes a pre-post intervention assessment of the HLE using LENA audio-recordings, which is an objective assessment and the research standard for measuring talk with children. These recordings will come from a small recorder (“talk pedometer”) children wear (in a shirt pocket) for a day at a time. See Section 8.1.2 for details about LENA assessment.

In line with emerging guidance on pilot studies prior to high-quality large-scale efficacy trials, the current study design does not include a control group. This is due to the high likelihood of an underpowered sample in this pilot to detect meaningful differences in the endpoints that will be evaluated in the large-scale RCT. By focusing the pilot on delivering TWMB in both clinics, we can maximize the number of dyads ( $n = 86$ , with goal of having at least 66 dyads able to enter phase II) to obtain a better estimate of variability in intervention response, rather than using resources to conduct underpowered difference tests between conditions for an untested intervention in this setting.

Site study teams will consent dyads and will complete baseline measures prior to the start of TWMB implementation in clinics (or prior to having a WCC visit with TWMB during the intervention period). To gather preliminary evidence that TWMB is effective for families with an inadequate HLE and to avoid ceiling effects in this small sample, we will enroll dyads with baseline LENA scores that are  $\leq 75^{\text{th}}$  percentile compared to age-referenced normative data. Of note, previous data have shown that without intervention, caregiver’s language-promotion behaviors do not show significant change across birth to 48 months of age. Therefore, evidence of change in caregiver’s language-promotion behaviors over the course of the TWMB pilot trial would be meaningful preliminary evidence of TWMB efficacy for the home language environment.

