### 9.2 SAMPLE SIZE DETERMINATION

The primary endpoint is a binary variable of reaching at least a 10% increase in AWC or CTC percentile scores from Baseline (Week 1) to Post-intervention (Week 48). This increase is based on previous language-promotion intervention studies using LENA, which reported statistically significant gains (for intervention versus control) for parent language-promotion behaviors ranging from 10-30%. In terms of clinical relevance, the proposed 10% gain in AWC would be an increase of ~160 adult words per hour, which equates to an increase of ~3 points in child language standard scores on the Bayley Scales of Infant Development and the Preschool Language Scale (proposed two-point increase for every increase of 100 adult words per hour for children age birth to four years-old).

The study is expected to have at least 70% of caregiver participants reaching improvement in language-promotion behaviors at the end of the study. In other words, the targeted rate of improvement in language-promotion behaviors is 70%. We plan a total accrual of up to 86 child-caregiver dyad participants into the study with a goal of having at least 66 dyads enter into phase II of the study. With an estimated phase II attrition rate of 20%, we expect that a total of 53 enrolled child-caregiver dyad participants will complete phase II of the study and hence the effective sample size is 53. Using a two-sided exact test with a significance level of 0.05, we are able to reach 85% power to reject a null rate of improvement at 50%, should the targeted rate of improvement be reached.

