#### 9.4.8 EXPLORATORY ANALYSES

We will examine barriers to enrollment, including our ability to contact caregivers, the proportion of caregivers that consent to participate in the study, enrollment of caregiver-child dyads, and caregivers' willingness to

complete baseline assessments. We will also examine characteristics related to attrition for caregiver and provider participants. Descriptive statistics will be used in these exploratory analyses.

Caregiver language promotion behaviors (LENA) will be examined and reported descriptively. Child vocalization scores (LENA) will be reported descriptively. We will also examine associations of differences in change in LENA scores with caregiver characteristics (e.g., low, or high baseline LENA scores, education level, SES) using analysis of variance (ANOVA) models or linear regression models.

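### Two LENA days are recorded at each time point, but no stated analysis separates day-to-day noise from response, and noise alone can meet the 10% responder criterion at a rate near or above the 50% null

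*Protocol*

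**What the plan says.** Protocol section 4.2.1 states that "the current study design does not include a control group" and explains that treating every dyad allows the team "to obtain a better estimate of variability in intervention response, rather than using resources to conduct underpowered difference tests".

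Section 8.1.2 asks for replicate days: "Families will complete a recording on two separate days during Baseline (i.e., Phase 1"), and the same again at Post-Intervention for dyads that continue. The completeness rule, written for Post-Intervention only, is "at least one usable recording (i.e., usable recording from one day of the two possible recording days"), obtained within two attempts. On data entry, "The site study team will enter LENA standard scores at Baseline and Post-Intervention assessments in the study database", covering daily AWC and daily CTC. No rule says how the two days become one score.

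Section 9.2 defines the primary endpoint as a "binary variable of reaching at least a 10% increase in AWC or CTC percentile scores from Baseline (Week 1) to Post-intervention (Week 48"). It targets a 70% rate against a null of 50%, with 53 dyads expected to complete. Section 9.4.2 reports the percentage with an exact confidence interval and allows an exact test of a hypothesized null rate. Section 9.4.8 adds that "Caregiver language promotion behaviors (LENA) will be examined and reported descriptively", with ANOVA or regression of change on caregiver characteristics. Section 9.4.1 leaves detail to a separate SAP. Section 5.1.2 lets only dyads with a baseline score at or below the 75th percentile continue.

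**The concern.** The spread of pre-to-post change in a single-arm study mixes true differences in response with recording noise from both time points. The same noise enters the responder classification, because a family whose behavior has not changed can still record a higher percentile on another day. The endpoint makes this easier: a rise on either of two scores counts, and if 10% is read as a relative rise, a dyad at the 20th percentile needs only 2 points (0.10 × 20).

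At stake is how the main result is read. A 50% null is informative only if clearly fewer than half of unchanged families would meet the criterion, and nothing in the protocol shows this. The planners of the later RCT would also not learn how much of the spread of change is day-to-day variation, which is what decides how many recording days to request. The repeated days that could answer both questions are already being collected.

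**Working it through.** **Plan's own figures.** The protocol gives no day-to-day variance or reliability, so there is no figure on this point to reproduce. Its effective sample size follows: 66 × 0.8 = 52.8, or 53. With n = 53, null 50% and two-sided exact α = 0.05, rejection in favor of improvement needs at least 35 responders (35/53 = 66%). The exact power at 70% is then 78.4%, whereas the stated 85% matches a normal approximation (85.1%). That is a separate matter, and only the count of 35 is used below.

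**Step 1: noise in the change score.** Set the single-day variance to 1. Let ρ be single-day reliability, τ the SD of true response, and k the number of days averaged at each time point. Both ρ and τ are assumptions.

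Var(change) = τ² + 2(1 − ρ)/k

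With ρ = 0.7 and τ = 0.3:
- One day per time point: 0.09 + 0.60 = 0.69; SD 0.83; noise share 0.60/0.69 = 87%.
- Two-day means: 0.09 + 0.30 = 0.39; SD 0.62; noise share 0.30/0.39 = 77%.

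Across ρ = 0.5 to 0.9 with τ = 0.3, the noise share runs from 92% down to 69% with one day and from 85% down to 53% with two. Averaging halves the noise variance but does not remove it.

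**Step 2: responders when nothing has changed.** A simulation of 400,000 dyads per setting applied the actual AWC-or-CTC percentile criterion with zero true change. Scores were normal, converted to percentiles; the AWC–CTC correlation was assumed to be 0.6; both baseline scores had to be at or below the 75th percentile. The share meeting the criterion was:

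| ρ (assumed) | 10% relative rise, one day | 10% relative rise, two-day means | 10-point rise, one day | 10-point rise, two-day means |
|---|---|---|---|---|
| 0.5 | 71.2% | 66.3% | 60.6% | 52.9% |
| 0.6 | 69.5% | 64.9% | 57.4% | 49.4% |
| 0.7 | 67.4% | 62.9% | 53.4% | 44.7% |
| 0.8 | 64.8% | 60.1% | 47.5% | 37.9% |
| 0.9 | 60.3% | 54.8% | 37.3% | 26.2% |

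If only one of the two baseline scores must meet the cutoff, the ranges are 49% to 64% (relative) and 24% to 55% (10 points). At ρ = 0.7 the SD of AWC percentile change is about 23 points with one day and 17 with two. These shares include regression to the mean from applying the cutoff to a noisy baseline.

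**Step 3: against the test.** At ρ = 0.7, expected responders among 53 unchanged dyads are 0.674 × 53 = 35.7 (relative, one day), 0.629 × 53 = 33.3 (relative, two-day), 0.534 × 53 = 28.3 (10-point, one day) and 0.447 × 53 = 23.7 (10-point, two-day). The 50% null corresponds to 26.5 and rejection to 35.

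**The case against.** Several objections have force.

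- **Combining days is SAP detail.** True of the averaging rule taken alone. But section 9.4.1 says the SAP will detail the analyses outlined in section 9.4, and none outlined there uses the repeated days. Whether both days reach the database separately must also be settled during data collection.
- **A reader might infer that the second day is discarded, or that single days will be analyzed.** The text supports neither. Two days are requested in each phase, daily scores are entered, and one usable day is only a minimum for Post-Intervention. What is missing is a stated use of the pair.
- **A reader might infer that the SD of change will be reported as response variability, and so overstated for the RCT.** No section commits to such a figure, and the phrase in 4.2.1 explains where resources go. An RCT using the same recordings needs the observed SD, noise included. In Step 1, planning on the noise-removed variance would understate it by a factor of 0.39/0.09 = 4.3.
- **Paired days do not isolate response.** Correct. They identify short-term noise only. Without a control group, natural change over 48 weeks and regression to the mean after the 75th-percentile cutoff remain.
- **Section 4.2.1 cites earlier data showing no significant change without intervention.** A stable group average does not limit how many individual dyads move by 10% through noise.
- **The size rests on assumptions.** It does. With high reliability, two-day means and a 10-point reading, the null share falls to 26%, well below 50%.

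**Conclusion.** The point holds as a gap between a stated aim and the stated analyses, and as a warning about the 50% null. With reliability of 0.5 to 0.9, AWC–CTC correlation of 0.6, no true change and both baseline scores at or below the 75th percentile, about 55% to 71% of dyads meet a 10% relative rise and 26% to 61% a 10-point rise. The relative reading puts the noise-only rate above the null throughout that range; the 10-point reading puts it on either side. None of these reliabilities comes from the documents, so the true rate is unknown, but the collected baseline pairs can inform it. This is a low-cost improvement worth making; it does not show that the primary analysis is invalid.

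**What to change.** 1. In 8.1.2, keep the two recording days as separate entries in the study database.
2. In 8.1.2 and 9.2, score each time point as the mean of all usable days, with the same rule at Baseline and Post-Intervention and a minimum of one day.
3. In 9.4.8, estimate the within-dyad day-to-day variance from dyads with two usable days. There are at most 86 baseline pairs, including dyads that do not continue, and about 53 post-intervention pairs if every completer has two usable days.
4. Beside the primary proportion, report the share of dyads whose second baseline day meets the same AWC-or-CTC 10% criterion relative to the first. Note that single-day pairs overstate the noise in two-day means.
5. Report the observed SD of change, which is the RCT planning input if the recording scheme is unchanged, together with its day-to-day component. Do not report a noise-removed SD alone.
6. State that natural change over 48 weeks and regression to the mean after the cutoff are not removed.

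The cost is a few lines of analysis text, one table, and a check that sites enter the days separately. No new recordings are needed.
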